### Recruitment

The recruitment period began in September 2025 and is expected to be concluded by August 2027. Recruitment strategies will include advertisements in local and regional newspapers, as well as on social media, with contact information provided for interested individuals. Additionally, the study will be publicized in primary health care units (Unidades Básicas de Saúde – UBS – in Portuguese). An initial telephone contact will be made, during which participants will receive information about the purpose of the study and undergo a preliminary screening to determine their eligibility. Eligible individuals will be invited to visit the Neuromuscular Assessment Laboratory (LabNeuro) of the ESEF/UFPel. During this visit, they will be received by one of the researchers in charge ([name] or [name]) who will provide detailed information about the research procedures, including potential risks and benefits, and will clarify any doubts. Finally, participants who agree to participate will be asked to sign an informed consent form in Portuguese, which will be obtained in person by the same trained researcher, and a copy of the signed form will be provided to each participant for their records.

### Randomization

The randomization sequence will be generated on the website www.random.org, with a 1:1:1 proportion and stratified by age group (60–67 and 68–75 years), and MMSE scores (categorized as with or without cognitive decline) by a researcher not involved with recruitment, data collection, or intervention. The sequence is based on randomly sized blocks that are not disclosed to ensure concealment.

### Allocation concealment mechanism

Upon enrollment in the study, each participant will be assigned an internal identifying number (ID) that will be used for the allocation sequence. A blinded researcher will implement the allocation after the conclusion of the baseline evaluation by accessing the randomization list based on the participants’ IDs. Participants will be allocated into one of the three groups (aquatic aerobic exercise program combined with cognitive tasks, conventional aquatic aerobic exercise program, or control group) and informed about their intervention via telephone or message.

### Implementation

[name] is the researcher responsible for generating the allocation sequence, [name] is the researcher responsible for enrolling participants, and [name] is the researcher responsible for assigning participants to interventions.

### Blinding

Blinding will be applied to outcome assessors and data analysts responsible for evaluating both primary and secondary outcomes. Due to the nature of the interventions, blinding is not feasible for the staff conducting the exercise sessions or the participants. To maintain assessor blinding, participants will be instructed not to disclose their group allocation or discuss intervention details during outcome assessments. In the case of unintentional unblinding for any reason, researchers involved will notify the steering committee. This information will be documented for internal control purposes.

### Data collection methods

During the first visit, after signing the consent form, participants will undergo an initial office blood pressure assessment. Afterward, they will complete self-reported questionnaires related to cognitive status, eating habits, mental health, self-perceived of cognitive function, physical activity levels, quality of life, and sleep quality.

On the second visit, participants will initially remain seated at rest for 10 min, during which heart rate variability will be measured. Following this resting period, office blood pressure will be assessed, and participants will proceed with the blood pressure and heart rate reactivity protocol using the Stroop test as a mental stressor. In the sequence, they will complete the cognitive assessments. Finally, anthropometric measurements will be taken, and functional tests will be performed.

All outcome assessments will be conducted by trained and experienced assessors using standardized procedures. The same researcher will apply each test at baseline, post-intervention, and follow-up assessments, with all evaluations conducted during the same time of day across time points to ensure consistency. Questionnaires will be administered individually in a private room to ensure participant comfort and confidentiality. The post-intervention assessments will begin 48 h after the last session. To minimize participant burden and optimize feasibility, the assessment protocol was pilot tested to refine test sequencing, rest periods, and overall logistics, ensuring efficient and standardized data collection.

All randomized participants will undergo outcome assessments, regardless of their participation status or completion. Participants who withdraw from the study at any time after randomization will still be invited to complete the final assessments and follow-up, ensuring inclusion of data in the intention-to-treat analysis.

#### Measurement of the primary outcome

##### Objective cognitive function

The COWAT will be used to assess verbal fluency as an aspect of executive function [44]. In this test, participants must say as many words as possible that start with the letters “F,” “A,” and “S” within 1 min for each letter. Proper names, repeated words, and variations in gender, number, and conjugation are not considered. A higher number of words in each test indicates better verbal fluency.

#### Measurements of secondary outcomes

##### Objective cognitive function

The DST-F will be used to assess attention span and short-term memory [45]. The test requires participants to verbally recall a sequence of numbers dictated by the examiner. It begins with three numbers ranging from 0 to 9, read at 1-s intervals, which participants must remember in the correct order. The sequence increases by one digit if pronounced correctly. If participants fail to recall the correct sequence twice in a row, the test ends. The number of digits correctly recalled is recorded as the test result, with a higher score indicating better performance.

The TMT will be used to assess different components of cognitive processing related to attention and executive functioning [46]. In the first part of the instrument (TMT–A), which measures visual attention and processing speed, participants must draw a line connecting the numbers 1 to 25 in ascending order. In the second part (TMT–B), which measures set-shifting ability (i.e., a core component of cognitive flexibility within executive function), participants connect numbers (1–13) and letters (A–L) in an interleaved numerical and alphabetical order. Participants are instructed to maintain pencil-and-paper contact throughout the test, and shorter completion times indicate better performance.

##### Self-perceived cognitive function

The Brazilian version of the Cognitive Failures Questionnaire (CFQ) will be used to measure the frequency of cognitive failures in everyday life, including lapses in attention, memory problems, and failures in executing intentional actions [47]. The questionnaire consists of 25 self-administered items, with responses on a Likert-type scale from 0 to 4, which assess the frequency of cognitive failures in different daily contexts. The total score ranges from 0 to 100 points, with higher scores indicating a greater perceived frequency of cognitive failures and, therefore, poorer self-perception of cognitive function.

##### Aerobic fitness

The 6MWT will be performed to measure aerobic fitness [48]. The course proposed in the original test is a 45.72 m rectangular course. The course will be adapted for a straight line of 30 m in length, demarcated with cones every 3 m. Participants are instructed to walk for 6 min in a flat 30 m course, where the total distance walked “as fast as possible” is assessed.

##### Lower limb strength

The 30-s Chair-Stand test will be performed to measure the strength of the lower limbs [48]. Participants are instructed to sit and stand up from a chair 43 cm high from the seat, without the aid of the upper limbs, as many times as possible for 30 s. The total number of complete repetitions performed within the 30 s is recorded as the result, with higher values ​​indicating greater lower body strength.

##### Upper limb strength

The Arm Curl test will be performed to measure the strength of the upper limbs [48]. Starting at full elbow extension and holding a 2 kg dumbbell in each hand, participants are instructed to perform the maximal number of elbow crunches over the full range of motion for 30 s. The test is performed with both upper limbs. The total number of complete repetitions performed within the 30-s time frame is recorded as the result, with higher values indicating greater upper body strength.

##### Lower limb flexibility

The Sit-and-Reach test will be performed using a Wells Bench to assess lower limb flexibility, particularly the hamstring and lower back muscles [49]. Participants sit barefoot on the floor with their legs extended and together, knees fully extended, and the soles of their feet flat against the front of the bench. With arms extended and hands overlapping, they slowly bend forward from the hips, sliding their hands along the measurement scale on the bench, without flexing the knees or using compensatory movements. The maximum reach is held for approximately 2 s, and the greatest distance reached in centimeters in three attempts is recorded.

##### Agility and dynamic balance

The TUG test will be performed to measure agility and dynamic balance. Participants are instructed to stand up from the chair (43 cm), turn around a marker that will be 3 m away, and return to the starting position. The shortest time of the two attempts is considered the result.

##### Dual-task performance

Dual-task performance involves simultaneously performing the TUG test and a cognitive task. Participants will be instructed to complete the TUG test while reciting alternating letters (e.g., A, C, E, etc.) [37]. The time taken for the TUG and the number of correctly recited letters are recorded as test results.

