Although the benefits of dual-task aquatic exercise for older adults are promising, it has not yet been proven whether the inclusion of cognitive tasks provides superior gains in cognitive function compared to the same aquatic exercise program alone. On the other hand, the inclusion of cognitive tasks could interfere with gains in physical fitness and associated mechanisms due to limited attentional capacity [41]. Moreover, little is known about how this approach may affect cardiovascular health and psychosocial outcomes, including symptoms of anxiety and depression, sleep quality, and quality of life. Additionally, the latest global consensus on exercise recommendations for older adults emphasizes that multicomponent interventions, which include cognitive tasks, contribute to improving cognition and functional capacity during aging [12]. Thus, interventions involving aquatic exercise programs that provide adaptations in various components of physical fitness, conducted in combination with cognitive tasks, emerge as an innovative strategy, aligned with current recommendations for healthy aging. Therefore, there is a lack of randomized clinical trials with high methodological rigor to clarify these issues, despite the importance of the topic for the health of older adults.

Therefore, we aim to examine the effects of a 12-week aquatic aerobic exercise program combined with cognitive tasks on cognitive function, physical function, cardiovascular, and psychosocial parameters in older women, compared to a conventional aquatic aerobic exercise program and a control group. We hypothesize that both exercise programs will significantly enhance the measured outcomes compared to the control group. Additionally, we expect the aquatic aerobic exercise program with cognitive tasks to have a more pronounced positive effect on cognitive function, as well as on cardiovascular and psychosocial parameters, compared to conventional aquatic aerobic exercise, with similar responses in physical function.

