### Outcomes

The primary outcome of the study is executive function (verbal fluency subtype), assessed by the Controlled Oral Word Association Test (COWAT; total F-A-S score), which captures aspects of inhibitory control, cognitive flexibility, and verbal initiation. The primary endpoint is the post-intervention time point. The primary analysis will focus on between-group differences at post-intervention, with additional longitudinal analyses examining changes from baseline and the maintenance of effects at follow-up (12 weeks after the end of the intervention).

The secondary outcomes of the study will be presented as group means and include:

Cognitive function, which will be assessed at baseline, post-intervention, and at the 12-week follow-up after the end of the intervention time points:Attention span and short-term memory, measured by the Digit Span Test – Forward (DST–F);Processing speed and visual attention, measured by the Trail Making Test – part A (TMT–A);Executive function (set-shifting ability), measured by the Trail Making Test – part B (TMT–B);Self-perceived cognitive failures, measured by the Cognitive Failures Questionnaire (CFQ).

Physical Function, which will be assessed at baseline and post-intervention time points:Aerobic fitness, measured by the 6-min Walk Test (6MWT);Lower limb strength, measured by performance in the 30-s Chair Stand Test;Upper limb strength, measured by performance in the Arm Curl Test;Lower limb flexibility, measured by the Sit-and-Reach Test (Wells Bench);Agility and dynamic balance, measured by performance in the Timed Up and Go (TUG) Test;Dual-task performance, measured using the TUG combined with a simultaneous cognitive task.

Cardiovascular parameters, which will be assessed at baseline and post-intervention time points:Office blood pressure, measured using a calibrated and automated oscillometric device;Heart rate variability, measured using a heart rate monitor;Blood pressure reactivity, measured using the auscultatory method during the Stroop Test for 3 min;Heart rate reactivity, measured using a heart rate monitor during the Stroop Test for 3 min.

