### Sample size

The sample size was calculated using G*Power 3.1 software, based on the study’s primary outcome, assessed by the COWAT, using unpublished data from our laboratory. An effect size of ƒ = 0.180 was used, with 90% power and an alpha of 5%. The calculation indicated a required sample of 84 participants, with an additional 20% added to account for potential dropouts, resulting in 102 participants to be recruited.

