### Statistical methods

Descriptive data will be presented as means with standard deviations and/or 95% confidence intervals, or as absolute or relative frequencies, when applicable. Generalized Estimating Equations (GEE) will be used to compare primary and secondary outcomes, assuming an unstructured working correlation matrix. In all GEE models, group and time will be treated as categorical variables, and group × time interactions will be included to test intervention effects. Bonferroni-adjusted post hoc tests will be applied when multiple comparisons are performed. The efficacy of the trial will be assessed using a single pre-specified primary outcome and a single primary comparison, consistent with SPIRIT recommendations for clinical trial protocols. Therefore, no multiplicity adjustment across outcomes will be applied. Analyses of secondary outcomes will be considered exploratory, and multiplicity adjustments will be applied only for multiple comparisons within the same outcome (e.g., Bonferroni-adjusted post hoc tests).

Both per-protocol (PP) and intention-to-treat (ITT) analyses will be conducted. In the analysis following the ITT principle, all randomized participants are analyzed in the group to which they were initially assigned, regardless of adherence, treatment receipt, or protocol deviations. Multiple imputations will be used to impute missing data using a specific function on SPSS software. Additionally, PP analyses will be performed to evaluate the robustness of the findings and the effect of adherence to the intervention. Therefore, participants must have at least 70% attendance during the 12-week intervention to be included in the PP analysis. This threshold was defined to ensure sufficient exposure to the training stimulus to plausibly induce adaptations, while accounting for the variability in attendance commonly observed in exercise interventions involving older adults. This cutoff has been adopted in previous aquatic exercise intervention studies conducted by our research group involving older populations under similar conditions [22].

No additional analyses, such as subgroup or sensitivity analyses, are planned for this trial. All statistical procedures will be performed in the SPSS vs. 28.0 program, and the significance level adopted is α = 0.05. Additionally, between-group effect sizes will be calculated using Cohen's d based on change scores and classified as small (≥ 0.2), moderate (≥ 0.5), or large (≥ 0.8) [60, 61].

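### The dual-task letter count is taken over a self-paced walk, so a faster TUG lowers it with no change in cognition; correct letters per second should be the cognitive result

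*Protocol article*

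**What the plan says.** The Outcomes section lists the test among the physical function outcomes, measured at baseline and post-intervention: "Dual-task performance, measured using the TUG combined with a simultaneous cognitive task". The section Dual-task performance gives the procedure, "Participants will be instructed to complete the TUG test while reciting alternating letters", and the scoring, "The time taken for the TUG and the number of correctly recited letters are recorded as test results". It sets no fixed recitation time, derives no rate, gives no direction for the count, and does not say how time and count are to be read together.

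For the single-task TUG, the section Agility and dynamic balance makes shorter better: "The shortest time of the two attempts is considered the result".

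The Statistical methods section covers the analysis: "Generalized Estimating Equations (GEE) will be used to compare primary and secondary outcomes, assuming an unstructured working correlation matrix". The models contain group, time and their interaction. No adjustment for the length of the walk is mentioned. The section Protocol and statistical analysis plan says that the article contains the analysis plan.

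**The concern.** A count of correct responses measures performance only when everyone has the same time in which to respond. Here the time is itself an outcome that the intervention is meant to shorten. The Background section states the expectation: "We hypothesize that both exercise programs will significantly enhance the measured outcomes compared to the control group". Those outcomes include the TUG. If the exercise arms walk faster, they have fewer seconds in which to recite, and their mean count drifts below control's for a purely mechanical reason. A group-by-time effect on the raw count could then be read as a cognitive cost of aquatic exercise.

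This matters because the test is the listed outcome that most directly combines motor and cognitive performance, and the combined programme is presented as training for such demands. If no rule is fixed in advance, the choice between count and rate would be made after the data are seen, and the two can point in opposite directions.

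**Working it through.** The documents give no figure for this outcome, so there is nothing to reproduce. The check is an identity plus a comparison with the protocol's other counts.

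**Inputs.** From the protocol: the two recorded results are dual-task TUG time T and the number of correct letters N. Assumed, because the protocol does not give them: T between 8 and 15 s, and a recitation rate r between 0.5 and 1.5 correct letters per second. The size of any change in T is also assumed.

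**Step 1. Effect of walking speed.** Expected count: N = r × T. If T falls by a fraction c and r is unchanged, the new count is r × T × (1 − c), so N falls by the same fraction c. This percentage does not depend on the assumed r and T.

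- Example: r = 1.0 per second and T = 10 s give N = 10. With T = 9 s, N = 9.0, a fall of 10% with no cognitive change.
- Ends of the assumed range, 10% faster: 4.0 falls to 3.6 (T = 8 s, r = 0.5), and 22.5 falls to 20.25 (T = 15 s, r = 1.5).

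**Step 2. Break-even gain in rate.** The count stays level only if r is multiplied by 1/(1 − c), that is, if the rate gain is 1/(1 − c) − 1.

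| Fall in TUG time | Change in count at the same rate | Rate gain needed to keep the count level |
|---|---|---|
| 5% | −5% | 1/0.95 − 1 = 5.3% |
| 10% | −10% | 1/0.90 − 1 = 11.1% |
| 15% | −15% | 1/0.85 − 1 = 17.6% |
| 20% | −20% | 1/0.80 − 1 = 25.0% |

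A real gain below break-even shows as a loss: with T down 10% and r up 5%, N = 10 × 0.90 × 1.05 = 9.45. A gain above break-even shows as a gain, only attenuated.

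**Step 3. The same cases scored as a rate.** N / T = r. With r unchanged, the change is 0% whatever the walking speed. With r up 5%, the rate shows +5%.

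**Step 4. Which comparisons are affected.** At a common rate, the ratio of two arms' counts equals the ratio of their times. If an exercise arm is 10% faster and control is unchanged, the ratio is 0.90. If both exercise arms are 10% faster, the ratio between them is 0.90/0.90 = 1, so the effect cancels. If one is 10% and the other 8% faster, it is 0.90/0.92 = 0.978, a difference of about 2%.

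**Step 5. Other counts in the protocol.** The COWAT allows one minute per letter, the chair stand and arm curl tests 30 s each, and Stroop errors are counted over 3 min. Each has a fixed window. The dual-task letter count does not.

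**The case against.** The strongest reply is that the text only records time and count as a pair. It does not label the count a cognitive score, give it a direction or say that it will be read without the time, and it lists the test under physical function. Anyone with both numbers can derive a rate, so no information is lost. Part of this stands: it is a scoring and reporting defect, and the data collection is sound. It does not remove the point. The chair stand and arm curl sections use the same kind of wording for their scored results, the GEE plan covers secondary outcomes without a term for duration, and the article says that it contains the analysis plan. Followed as written, the raw count is a result to be compared between groups.

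A second reply is that strict proportionality needs a constant recitation rate. The protocol's Discussion argues that motor and cognitive demands share limited attention, so the rate may change with walking speed. That is fair, and it is a reason to measure the rate directly: the raw count mixes any such change with the length of the walk.

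Three stronger readings are tempting, and the documents do not support them:

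- A reader might infer that the count falls even when cognition improves. That holds only while the rate gain is below the break-even values.
- A reader might infer that the trial would wrongly find no added benefit of cognitive tasks over conventional exercise. The Background and Discussion expect similar physical gains in the two exercise arms, in which case the effect largely cancels between them.
- A reader might infer that dual-task TUG time is also invalid and should give way to a dual-task cost relative to single-task TUG. Dual-task time is a legitimate functional outcome in a randomized comparison, and the cost ratio has a directional problem of its own. For illustration, if single-task time goes from 8 to 7 s and dual-task time from 10 to 9 s, both improve, yet the cost rises from (10 − 8)/8 = 25% to (9 − 7)/7 = 28.6%.

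**Conclusion.** The point holds for the raw letter count. At an unchanged recitation rate the expected count falls by the same percentage as the TUG time, so comparing raw counts can show an apparent cognitive loss in the exercise arms against control where none exists. The percentages follow from count = rate × time and do not depend on the assumed times and rates. The actual size in this trial depends on how much faster the exercise arms become and on whether the rate stays constant, and the protocol gives neither.

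The reach is limited to one component of one secondary outcome in a family declared exploratory. The primary COWAT outcome uses fixed one-minute windows and is untouched. The change is worth making because the distortion is tied to treatment and is cheap to remove.

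**What to change.** In the Outcomes and Dual-task performance sections, before any unblinded analysis:

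1. Define the cognitive component of the dual-task test as correct letters per second: the number of correct letters divided by dual-task TUG time, both from the same attempt. Say which attempt is scored, since a rule is given only for the single-task TUG.
2. Analyse and report this rate alongside dual-task TUG time, which remains an outcome in its own right. State the direction of each: a higher rate is better, a shorter time is better.
3. Keep the raw count as descriptive.
4. Dual-task cost relative to single-task TUG may be added as an optional description. It should not replace dual-task time.

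Cost: one derived variable and a few lines of text. Count and time are already recorded, so no change in data collection is needed.
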